## Results

For this report, we present data from our pilot data which include 30 participants (n=30) of 2 groups of children with controlled ethnicity (Filipino) but living in different physical environments (urban and rural settings) during the resting baseline phase of our experimental paradigm. The pilot samples are controlled for gender and age-matched. Table 1 presents a summary of the demographics and statistics of the variables included in the analysis for this paper.

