#### Statistical Data

Descriptive statistics involving measures of central tendencies, variation, and dispersion are used to describe the salient characteristics of the data gathered. Demographic data related to participant gender, age, BMI, type of school (ie, public, private), number of parents working, primary caregiver, highest educational attainment of caregiver, family income, and parent’s occupation will be gathered and considered in further statistical analyses. The Shapiro-Wilk test of normal is used to determine normality at baseline of the characteristics of the participants included in the study. Univariate and multivariate tests are likewise used to determine whether there are group and subgroup baseline similarities at critical alpha=.05. Variables deemed as non-normally distributed or significantly different at baseline are used as covariates. General linear modeling is used to determine whether effects of ethnicity or environment (used as the independent variables [IV] in this study) can explain differences in the behavioral measures of the participants at a critical value of alpha=.05. Autonomic regulation is represented in this research as HF (n.u.) and LF (n.u.) of HRV and mean EDA (SCL/SCR) values as multivariates. Multivariate analysis of variance (MANOVA) tests will be used to determine whether effects of ethnicity or environment (used as IV in this study) can explain differences in the multivariate set of DVs, across the different research aims, with the different pairwise combinations in between 3 events (resting baseline, stimulation, and recovery). Effect size is interpreted using the values of Cohen *d*. Statistical analysis will be computed using SPSS version 23.0.

Specific to this report, sample size and power analysis are performed using G*Power version 3.1.9.2 [91,92]. Post hoc analysis of computed achieved power of the pilot data will be ascertained to determine the needed effect size for a subsequent a priori computation of required sample size for MANOVA tests.

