### Group Differences: MANOVA

Preliminary data from 30 gender-controlled and age-matched participants with a mean age of 8.667 (SD 1.759) are analyzed for the influence of physical environments on the neurophysiological regulation of response to sensory stimuli using the HF (n.u.) and LF (n.u.) bands of HRV and EDA-SCL during the resting baseline condition as DVs. On the basis of the Shapiro-Wilk test and independent samples *t* test, BMI was normally distributed (*P*=.149) and similar at baseline (*P*=.57) between urban- and rural-dwelling participants.

The mean HF (n.u.) for the resting baseline condition was computed at 62.301 (SD 15.903) for urban-dwelling children, which is higher than the rural-dwelling group (mean 52.096, SD 15.125). This is the other way around for the LF (n.u.), where the rural-dwelling group (mean 29.228, SD 10.639) fared better than the urban-dwelling group (mean 24.171, SD 9.370). EDA-SCL showed almost similar values, with the urban group having slightly higher values (mean 1.929, SD 0.600) compared with their rural group (mean 1.900, SD 0.363).

**Table 1 table1:** Summary of demographics and statistical results.

Demographics		Urban (N=15)	Rural (N=15)	Total (N=30)	Shapiro-Wilk test	*t* test	*F* test			
							Pillai *V*	*F*	*P*	*d*

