**Output**		
	Noncentrality parameter *λ*	16.5000
	Critical *F*	1.9171
	Numerator df	9.0000
	Denominator df	252.0000
	Total sample size	88
	Actual power	0.8094
	Pillai *V*	0.1765

^a^Computation was based on *F* tests–MANOVA: Global effects with analysis of a priori to compute for the required sample size.

^b^This is the critical value.

^c^This is the specific formula to compute for the power.

Using physical environment (urban or rural setting) as IV and the values at resting conditions of the LF (n.u.), HF (n.u.), and SCL as DV, a multivariate analysis of covariance (MANCOVA) test, specifically Pillai *V*, was performed using BMI as a covariate. In the series of analyses of variance (ANOVAs) performed, results of the multivariate tests confirm that the differences in the measures of autonomic regulation considered as DV among the 2 sampled ethnic groups in this study are not significant using a critical alpha of .05 (*V*=0.107, *F*_3,26_=1.033, *P*=.39, *d*=0.692). A univariate analysis of individual DVs reveals similar nonsignificant differences between LF (n.u.) (*F*_1,30_=1.909, *P*=.18, *d*=.523), HF (n.u.) (*F*_1,30_=3.243, *P*=.08, *d*=0.681), and SCL (*F*_1,30_=0.025, *P*=.87, *d*=0.063) of the sampled groups. It remains unclear whether the sample size in our pilot findings confounded the influence of the physical environment of the participants in explaining differences in the autonomic regulation of response to sensory stimuli.. Thus, a subsequent power analysis of the sample reported is performed.

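### The pilot groups were age-matched and gender-controlled, but the reported tests and post hoc power carry no age or gender term, and the covariate rule does not ensure that they enter

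*Protocol article*

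**What the plan says.** The Results describe a pilot of 15 urban and 15 rural Filipino children and state: "The pilot samples are controlled for gender and age-matched". The section on group differences repeats this. Table 1 gives the same age mean and SD, 8.667 (1.759), in both groups, with 1.000 in the *t* test column.

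The baseline comparison of BMI is unpaired ("On the basis of the Shapiro-Wilk test and independent samples" *t* test). The multivariate test has physical environment as the factor and HF, LF and SCL as outcomes, and "was performed using BMI as a covariate". No age term, gender term or matched-set term is reported. The printed result is V=0.107, F=1.033 on 3 and 26 df, P=.39. The Power and Sample Size Analysis section then reports f²=0.120 and power 0.283 for n=30.

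For covariates in general, the Statistical Data section says: "Variables deemed as non-normally distributed or significantly different at baseline are used as covariates".

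**The concern.** Balancing groups on age and gender removes those variables from the group difference. If they also predict HF, LF or SCL, that outcome variance remains in the error term unless the model includes them. The unadjusted test is then less precise than the design allows, and its P values and power do not reflect the balancing.

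The covariate rule does not guard against this. Matching forces the baseline comparison of age to show no difference, so age cannot enter by that route. The other route depends on the shape of the variable's distribution, which says nothing about its relation to the outcome. The article reads its null pilot result as a lack of power, so the size of the error term bears on that reading. The same rule governs the planned four-group analyses.

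**Working it through.** **Are the printed figures from an independent-groups analysis?** The inputs are the Table 1 means and SDs with n=15 per group. The formula is F = (difference)² / [(SD₁² + SD₂²)/15].

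- HF: difference 62.301 − 52.096 = 10.205; SE = √[(15.903² + 15.125²)/15] = 5.667; t = 1.801; F = 3.243, P = .083 on 28 df. Printed: 3.243, P=.08.
- LF: difference 5.057; SE 3.660; F = 1.909, P = .178. Printed: 1.909, P=.18.
- SCL: difference 0.029; SE 0.181; F = 0.026, P = .874. Printed: 0.025, P=.87.
- BMI: unpaired *t* test P = .572, as printed.

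Multivariate: F = [V/(1−V)] × 26/3. V = 0.1065, which rounds to the printed 0.107, gives F = 1.033 and P = .394, as printed. The error df of 26 are those of a plain two-group model. Even the BMI covariate that the text names would reduce them to 25.

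Post hoc power: λ = 30 × 0.120 = 3.6 with noncentral F on 3 and 26 df gives 0.2836 (printed 0.283).

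So every printed figure is that of two unrelated groups with no age or gender term.

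**What would adjustment change?** Let R² be the share of within-group outcome variance that age and gender explain. It is taken as equal for the three outcomes and is an assumption, since the article gives no value. Age and gender are balanced, so the group difference is unchanged and f² becomes 0.120/(1−R²). Two covariates (BMI left out, as in the printed df) leave 3 and 24 df in the pilot, and 3 and 58 df for a two-group comparison at 32 per group (64 children, unadjusted 3 and 60 df). Power uses λ = N × f². For the observed pilot test, F = [0.1192/(1−R²)] × 24/3, where 0.1192 = 1.033 × 3/26.

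| Model | f² | Pilot P | Pilot power | Power, 32 per group |
|---|---|---|---|---|
| Unadjusted | 0.120 | .394 | 0.284 | 0.603 |
| Adjusted, R²=0 | 0.120 | .431 | 0.280 | 0.602 |
| Adjusted, R²=0.1 | 0.133 | .385 | 0.309 | 0.653 |
| Adjusted, R²=0.2 | 0.150 | .334 | 0.345 | 0.710 |
| Adjusted, R²=0.3 | 0.171 | .278 | 0.390 | 0.773 |

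**If the children were in fact paired one to one** (not stated), a matched-pair Hotelling T² has 3 and 12 df and T² is divided by (1−ρ), with ρ the assumed within-pair correlation. Pilot power is 0.244 (ρ=0), 0.269 (0.1), 0.338 (0.3) and 0.459 (0.5). The multivariate P is .446, .402, .301 and .182.

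**Does the sample size depend on this?** Table 2 uses f²=0.0625, four groups and three outcomes. λ = 88 × 3 × 0.0625 = 16.5 with 9 and 252 df gives power 0.8094 and N=88, as printed. The pilot f² of 0.120 is not an input.

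**The case against.** Several stronger readings are tempting, and the article does not support them.

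- *The covariate rule can never admit a matched variable.* It can. A non-normally distributed variable also qualifies, and Table 1 shows no Shapiro-Wilk result for age. The Statistical Data section also says that demographic data, including age and gender, will be considered in later analyses, though not how. Nor was the rule applied strictly: BMI met neither criterion (P=.149 for normality, P=.57 for the group difference) and is still the named covariate.
- *The paired test is the right one, and the HF result would be significant.* Identical age means and SDs fit frequency matching as well as one-to-one pairs. The HF P value falls below .05 only at an assumed ρ of about 0.3 (P=.049; it is .079 at 0.1). At ρ of 0 to 0.1 pairing loses power against the unpaired 0.284. The article claims nothing from HF.
- *The pilot conclusion or the sample size is wrong.* The multivariate P stays above .05 and pilot power below 0.80 at every value shown, and Table 2 does not use the pilot effect.
- *The main study wastes its matching.* It is not described as matched on age or gender. The Participants section gives only an age range and both sexes.

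It is also fair to say that leaving out a balanced predictor tends to make the test conservative, so no false positive claim is at risk. All of this stands. It limits the size of the point but does not answer it: the pilot was balanced on two variables that the analysis leaves out, and the rule selects covariates on grounds unrelated to the outcome.

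**Conclusion.** The point holds in a limited form. That the analysis was unpaired and unadjusted rests on exact reproduction of the printed figures and needs no assumption. The loss of precision does rest on an assumption, the variance explained by age and gender. If it is nil, nothing is lost by the present analysis. At 10-30%, adjustment raises pilot power from 0.284 to between 0.31 and 0.39, and power at 32 per group from 0.60 to between 0.65 and 0.77 for a two-group comparison at f²=0.12 with the groups balanced on both variables. The pilot stays non-significant and underpowered, and N=88 does not move. This is a low-cost improvement in how covariates are fixed, together with a restatement of exploratory pilot figures.

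**What to change.** In the Statistical Data section, enter age (continuous) and gender as fixed covariates in every MANOVA, whatever their normality or baseline tests show, and exempt both from the covariate selection rule. State whether the pilot children were matched one to one or by frequency. Restate the pilot F, df, P and post hoc power from the adjusted model, and say whether BMI is in it, so that the df agree with the model described. Use a matched-pair analysis (3 and 12 df in the pilot) only if children were paired one to one.

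The cost is a wording change, a re-run on data already collected, and two error degrees of freedom: at most 0.284 to 0.280 in pilot power and 0.603 to 0.602 at 32 per group. Table 2 needs no change on this account.

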### Group Differences: MANOVA

Preliminary data from 30 gender-controlled and age-matched participants with a mean age of 8.667 (SD 1.759) are analyzed for the influence of physical environments on the neurophysiological regulation of response to sensory stimuli using the HF (n.u.) and LF (n.u.) bands of HRV and EDA-SCL during the resting baseline condition as DVs. On the basis of the Shapiro-Wilk test and independent samples *t* test, BMI was normally distributed (*P*=.149) and similar at baseline (*P*=.57) between urban- and rural-dwelling participants.

The mean HF (n.u.) for the resting baseline condition was computed at 62.301 (SD 15.903) for urban-dwelling children, which is higher than the rural-dwelling group (mean 52.096, SD 15.125). This is the other way around for the LF (n.u.), where the rural-dwelling group (mean 29.228, SD 10.639) fared better than the urban-dwelling group (mean 24.171, SD 9.370). EDA-SCL showed almost similar values, with the urban group having slightly higher values (mean 1.929, SD 0.600) compared with their rural group (mean 1.900, SD 0.363).

**Table 1 table1:** Summary of demographics and statistical results.

Demographics		Urban (N=15)	Rural (N=15)	Total (N=30)	Shapiro-Wilk test	*t* test	*F* test			
							Pillai *V*	*F*	*P*	*d*
**Type of school, n (%)**										
	Public school	12 (80)	N/A^b^	N/A						
	Private school	N/A	15 (100)	17 (57)						
**Number of parents working, n (%)**										
	Both parents	10 (67)	13 (87)	23 (80)						
**Primary caregiver, n (%)**										
	Mother	13 (87)	12 (80)	25 (83)						
**Primary caregiver’s highest educational level, n (%)**			College degree	College degree						
	College degree	8 (53)	10 (67)	18 (60)						
Age in years, mean (SD)		8.667 (1.759)	8.667 (1.759)	8.667 (1.759)		1.000				
BMI^c^, mean (SD)		16.145 (3.722)	15.467 (2.683)	15.806 (3.207)	0.149	0.572				
HF (n.u.)^d^, mean (SD)		62.301 (15.903)	52.096 (15.125)	57.199 (16.108)	0.504		0.107	1.033	.394	0.692
LF (n.u.)^e^, mean (SD)		24.171 (9.370)	29.228 (10.639)	26.700 (10.181)	0.448					
SCL^f^ (µS), mean (SD)		1.929 (0.600)	1.900 (0.363)	1.914 (0.488)	0.397					

^a^N/A: not applicable.

^b^BMI: body mass index.

^c^HF (n.u.): high frequency (normalized unit).

^d^LF (n.u.): low frequency (normalized unit).

^e^SCL: EDA-Skin Conductance Level.

**Table 2 table2:** Sample size analysis protocol.

Analysis^a^		Results
**Input**		
	Effect size *f*^2^(*V*)	0.0625
	α err prob^b^	0.0500
	Power (1- *β* err prob)^c^	0.8000
	Number of groups	4
	Response variables	3
**Output**		
	Noncentrality parameter *λ*	16.5000
	Critical *F*	1.9171
	Numerator df	9.0000
	Denominator df	252.0000
	Total sample size	88
	Actual power	0.8094
	Pillai *V*	0.1765

^a^Computation was based on *F* tests–MANOVA: Global effects with analysis of a priori to compute for the required sample size.

^b^This is the critical value.

^c^This is the specific formula to compute for the power.

Using physical environment (urban or rural setting) as IV and the values at resting conditions of the LF (n.u.), HF (n.u.), and SCL as DV, a multivariate analysis of covariance (MANCOVA) test, specifically Pillai *V*, was performed using BMI as a covariate. In the series of analyses of variance (ANOVAs) performed, results of the multivariate tests confirm that the differences in the measures of autonomic regulation considered as DV among the 2 sampled ethnic groups in this study are not significant using a critical alpha of .05 (*V*=0.107, *F*_3,26_=1.033, *P*=.39, *d*=0.692). A univariate analysis of individual DVs reveals similar nonsignificant differences between LF (n.u.) (*F*_1,30_=1.909, *P*=.18, *d*=.523), HF (n.u.) (*F*_1,30_=3.243, *P*=.08, *d*=0.681), and SCL (*F*_1,30_=0.025, *P*=.87, *d*=0.063) of the sampled groups. It remains unclear whether the sample size in our pilot findings confounded the influence of the physical environment of the participants in explaining differences in the autonomic regulation of response to sensory stimuli.. Thus, a subsequent power analysis of the sample reported is performed.

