**Methods:**

In this study, we intend to recruit 128 children from different ethnic groups or environment contexts as follows: (1) 32 typically developing Chinese children living in Hong Kong; (2) 32 typically developing Filipino children living in Hong Kong; (3) 32 typically developing Filipino children who are living in urban areas; and (4) 32 typically developing Filipino children who are living in rural areas in Philippines. Autonomic activity (heart rate variability [HRV] and electrodermal activity [EDA]) will be measured and recorded using Polar H2 heart rate monitor and eSense GSR skin response sensor. Autonomic activity (HRV-low frequency, HRV-high frequency, and EDA) at different conditions between pairwise groupings will be tested using multivariate analysis of variance (MANOVA). All significant levels will be set at *P* ≤.05.

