### Power and Sample Size Analysis

A post hoc analysis using the results of the MANOVA test for the reported sample population on our preliminary data was conducted using G*Power version 3.1.9.2. Statistical power was computed using a sample of n=30 and the identified 3 DVs at resting baseline condition. Alpha level was set at alpha=<.05. The results of our post hoc analyses suggest that our effect size (*f*^2^=0.120) is considerably in the medium range [93], whereas power was low at 0.283. This is considerably different from the initial set sample size of n=32 (alpha=.05, *d*=0.80, *P*=.80). With this in mind, we then recomputed the required sample size using a priori methods, setting a moderately large effect size of *f*^2^=0.625 and a power of 0.80 for the needed 4 groups among 3 response variables to be used as DVs. Our post hoc analysis suggests that the current samples (n=15 per group) included in our pilot findings are underpowered; hence, significant effects may not yet be seen. On the basis of our results, the needed sample for this research is computed at n=22 per group (Table 2).

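### The 0.81 power at 22 per group belongs to one global four-group MANOVA; the planned two-group MANOVAs do not have 80% power at that size under the pilot effect

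*Protocol article*

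**What the plan says.** The footnote to Table 2 identifies the calculation as "MANOVA: Global effects with analysis of a priori to compute for the required sample size". The inputs are f²(V) = 0.0625, alpha 0.05, power 0.80, 4 groups and 3 response variables. The outputs are λ = 16.5, critical F = 1.9171 on 9 and 252 df, N = 88, actual power 0.8094 and Pillai V = 0.1765. The Power and Sample Size Analysis section concludes that "the needed sample for this research is computed at n=22 per group".

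The planned analysis is described differently. The Abstract says autonomic activity "at different conditions between pairwise groupings will be tested using multivariate analysis of variance (MANOVA"), with significance at .05 or below. Statistical Data plans MANOVAs "across the different research aims, with the different pairwise combinations in between 3 events (resting baseline, stimulation, and recovery"). Each of the four hypotheses under Research Hypothesis, and each comparison under Participants, sets two groups against each other. The article's pilot analysis is itself a two-group test on three responses, with a reported power of 0.283 at 15 per group. The Abstract and Participants still give 32 per group (128 in total).

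**The concern.** The power statement and the analysis refer to different tests. A global four-group test asks whether any of the four groups differ on the three responses, and it uses all 88 children. Each planned comparison uses only two groups, which is 44 children at 22 per group.

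One stated aim of the article is to settle the sample size of the main study, and the Discussion says the researchers will be guided by the result. If 22 per group is adopted in the belief that each hypothesis has 80% power, a null result on ethnicity, geographic environment or physical environment will be read as more informative than it is.

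**Working it through.** **Inputs.** From Table 2: f² = 0.0625, alpha = 0.05, k = 4 groups, p = 3 responses, N = 88, V = 0.1765. From Power and Sample Size Analysis: pilot f² = 0.120, power 0.283 at 15 per group. From the Abstract and Participants: 32 per group.

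**Formulas** (MANOVA global effects, Pillai V): s = min(k−1, p); df1 = p(k−1); df2 = s(N−k−p+s); λ = f² × N × s; power from the noncentral F.

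**Step 1, reproduce Table 2.** With k = 4, s = 3: df1 = 9, df2 = 3 × (88−4−3+3) = 252, λ = 0.0625 × 88 × 3 = 16.5, critical F = 1.9171, power = 0.8094. This matches exactly, so the 0.81 is the power of the four-group test.

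**Step 2, reproduce the pilot power.** With k = 2, s = 1, N = 30: df = 3 and 26, λ = 0.120 × 30 = 3.6, power = 0.2836 (stated 0.283). The article has therefore already used the two-group formula.

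**Step 3, apply the two-group formula to the planned tests.** With k = 2, s = 1, df = 3 and N−4, λ = f² × N. At 22 per group, N = 44, df = 3 and 40, critical F = 2.839. At 32 per group, N = 64, df = 3 and 60, critical F = 2.758. Three assumptions for the effect in a pair:

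| Assumed pair effect | f² | λ at 22 | Power at 22 | λ at 32 | Power at 32 |
|---|---|---|---|---|---|
| Pilot estimate | 0.120 | 5.28 | 0.42 | 7.68 | 0.60 |
| Table 2 effect spread evenly over six pairs | 0.125 | 5.50 | 0.44 | 8.00 | 0.62 |
| Table 2's full V in one pair, 0.1765/(1−0.1765) | 0.214 | 9.43 | 0.69 | 13.72 | 0.87 |

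For the second row, λ/N in Table 2 is 16.5/88 = 0.1875. With four equal groups the squared distances D² over the six pairs sum to 16 × 0.1875 = 3.0, a mean of 0.5. The pair λ is (n/2) × D², that is 11 × 0.5 = 5.5 or 16 × 0.5 = 8.0, equivalent to f² = D²/4 = 0.125.

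**Step 4, what 80% would require.** At the pilot f², 48 per group. At a fixed size, the f² detectable with 80% power is 0.27 at 22 per group (λ = 12.03, divided by 44) and 0.18 at 32 per group (λ = 11.64, divided by 64).

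**Step 5, uneven patterns.** Table 2's total effect is kept and only the pattern of group means is varied.
- Equally spaced means: the extreme pair has D² = 1.35, so λ = 14.85 and power 0.88 at 22 per group. Adjacent pairs have D² = 0.15, λ = 1.65 and power 0.15.
- One group apart from the other three: each affected pair has D² = 1.0 and power 0.76 at 22, 0.92 at 32.
- Two groups against two: each cross pair has D² = 0.75 and power 0.62 at 22, 0.81 at 32.

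At 22 per group the six pair λ values sum to 11 × 3.0 = 33. Each pair needs 12.03 for 80% power, and 3 × 12.03 = 36.1 exceeds 33. No pattern can therefore give three or more pairs 80% power at that size.

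**The case against.** Several points on the other side stand.

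- The article does not say how the four-group effect is distributed, so no single pairwise power is implied. Some patterns take individual pairs above 0.80. At 32 per group, if the urban Filipino group alone differed, all three distinct pairs listed under Participants would reach 0.92. The figures above are conditional on their assumptions.
- Two-group power of 0.23 at 22 per group might be inferred by carrying f² = 0.0625 straight over. That is not supported as Table 2's effect: there the value is per dimension with s = 3, and reusing it with s = 1 drops a factor of three from λ. Nor is it right to say that every planned test has less than half the claimed power, since 0.42 and 0.44 are just over half of 0.80.
- The 32 per group has a basis of its own: Participants cites an effect size of 0.8 for group differences from a previous study. That is a standardised difference, not a MANOVA effect. If it is read, as an assumption, as a multivariate distance, f² = 0.8²/4 = 0.16 and power is 0.55 at 22 and 0.74 at 32.
- A reader might add that twelve tests (four comparisons, three conditions) at .05 give a 46% chance of some false positive (1 − 0.95^12). That assumes independence. The tests share children and groups, Participants lists one pair twice, and the study calls itself exploratory. The figure is at most illustrative and the point does not rest on it.
- The Statistical Data wording about pairwise combinations across three events is loose, but the Abstract, Research Hypothesis and Participants make the two-group comparisons clear.

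The text's effect size, "0.625 and a power of 0.80 for the needed 4 groups among 3 response variables to be used as DVs", does not rescue the claim. With f² = 0.625 the four-group calculation would need about 12 children in total, not 88, so it looks like a slip for Table 2's 0.0625.

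**Conclusion.** The point holds. Table 2 is computed correctly, but for a test the article does not plan. The statement that 22 per group is needed for 80% power is not true of the two-group MANOVAs that carry the hypotheses. Under the pilot effect their power is 0.42 at 22 per group and 0.60 at 32. Under the other two readings of Table 2's effect it is 0.44 to 0.69 at 22 and 0.62 to 0.87 at 32. These figures assume equal groups, three responses, no covariates, alpha .05 per test and no loss of recordings. The fault is a mismatch between sample size and analysis, not an arithmetic error. The exploratory aim softens the consequences but does not make the 80% statement correct.

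**What to change.** In Power and Sample Size Analysis and in Table 2:

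1. State that the 80% applies only to the global four-group test.
2. Report the power of a two-group MANOVA, or the effect detectable with 80% power, at the sample size actually used, and name the assumed pair effect. The detectable f² is 0.27 at 22 per group and 0.18 at 32.
3. Reconcile 22 per group with the 32 per group in the Abstract and Participants, and the 0.625 in the text with the 0.0625 in Table 2.
4. Do not claim 80% power for the pairwise hypotheses.

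Optionally, add the global four-group test to Statistical Data so that the powered test is actually run, with the planned pairs as follow-up contrasts. This aligns the analysis with the calculation but does not raise pairwise power. Reaching 80% per pair at the pilot effect would take about 48 per group, or 4 × 48 = 192 children.

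Items 1 to 4 cost wording and a re-run of the power program. They need no extra children, but the stated power becomes less favourable.
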